### 3.5 Methodology for Aim3

(Test feasibility and impacts of the adapted version of IPT-G and mhGAP-IG).

To evaluate implementation-effectiveness of the mhGAP-IG (including IPT-G), we will apply a *hybrid effectiveness-implementation design* (79) and *randomized control trial (RCT)*. The evaluation constructs will be guided by the *Conceptual model of Implementation Research* (Figure 2) (56), which consider implementation, service, and patient outcome indicators. Primary outcomes will be focus on acceptability, engagement with the interventions, and effectiveness on adolescents' depression.

**Data Collection Measures, and Procedure.** The 2 MCH clinics that we build capacity in Aim 2 will be the pilot Implementation sites. During the 1st implementation cycle (about 2-3 months), we will work with only 1 MCH clinic (Cohort 1), and then work with another MCH clinic in the 2nd implementation (Cohort 2). For each cohort, 45 pregnant adolescents with moderate to severe depression will be recruited.

**Intervention Implementation.** Considering high prevalence of adolescent pregnancy, high risk for depression in this population, and low resource in MCH clinics, the WHO recommended full version of G-IPT may not be practical in meeting population service demands and needs. Therefore, we will test a Mini version of G-IPT. Recruited participants will be randomly assigned (using computer random generator by research staff) to three intervention arms—IPT-G full, IPT-G mini, and wait-list control, n=30 for each arm).

- **The IPT-G full and mini groups** will receive the assigned interventions (8 vs. 4 sessions) developed from Aims 1 & 2 (including a perinatal depression educational material/handout). To avoid contamination, intervention for the IPT-G full and mini versions will be carried out by 2 separate implementation teams (2-3 facilitators in each team) follow the assigned manual/protocol. Table 1 below provides intervention contents for the mini version, in comparing to the recommended long version. We will study implementation-effectiveness for both versions.
- **The Control** will receive standard care (with referral) and perinatal depression educational materials for safety concerns that we would have adapted from HAT work carried out in Aim 2. They will receive *IPT-G mini* after the post implementation assessment is completed.

**Table 2. Intervention content by session and overview of full versus mini versions of G-IPT**

| IPT-G Full Version
(8 sessions)                                                                                                                                                                      | IPT-G Mini Version
(4 sessions)                                                                                                                                                                      |
|-----------------------------------------------------------------------------------------------------------------------------------------------------------------------------------------------------------------|-----------------------------------------------------------------------------------------------------------------------------------------------------------------------------------------------------------------|
| 1. Recognize and start dealing with current depression                                                                                                                                                          | 1. Reviewing the context of depression, understanding interpersonal basis of depression, problem-solving, communication analysis and evaluation                                                                 |
| 2. Understand links between current depression and IPT problem areas; conduct an Interpersonal inventory                                                                                                        |                                                                                                                                                                                                                 |
| 3. Decide with the person on the interpersonal problems that are linked to the current depression, invite the person to join the IPT group and discuss goals and rules                                          | 2. Reviewing symptoms and functioning, understanding- grief, disputes and transitions especially arrival of baby and changes in body and social role, learning strategies to deal with these and evaluation     |
| 4. Introduce the group members and talk about depression                                                                                                                                                        |                                                                                                                                                                                                                 |
| 5. Discussion depression and the IPT problem areas – grief, role transitions and role disputes that the group members are facing                                                                                | 3. Reviewing symptoms and functions, preparing for birth and making plans for baby and self-care, understanding value of communication and support, reviewing depression and evaluation                         |
| 6. Discuss how the group will work on those areas                                                                                                                                                               |                                                                                                                                                                                                                 |
| 7. Use strategies specific to each IPT problem area                                                                                                                                                             | 4. Reviewing symptoms and functioning, identifying interpersonal strengths, support and strengthening communication, health facility engagement, plans for post baby and mother care, and depression evaluation |
| 8. Review what has happened during treatment, and for group members to say goodbye to each other and the facilitator. make plans about how to address problems that might arise up or new problems that emerges |                                                                                                                                                                                                                 |

Measures and Procedure. To evaluate implementation and effectiveness outcome, a mixed methods data collection approach will be applied, and data will be collected from multiple sources (i.e., implementers, MCH leaders, adolescent mothers and their family members) to minimize data collection bias. Three areas of outcomes will be evaluated (see Table 2). Both *quantitative data* (focusing on adolescent mothers' effectiveness outcomes, implementation fidelity, and MCH service outcomes) and *qualitative data* (focusing on implementation process and contextual factors that influence implementation and experience) will be collected through focus groups (2 groups for each intervention arm) at the end of implementation cycle.

All study participants will complete a baseline (Time 1) interview before randomization and implementation, followed by a 1 or 2-month implementation period (2 months for the IPT-G full and 1 month for the IPT-G mini). They will receive a post-intervention interview assessment at the end of implementation cycle (Time 2, about 3-4 months after the Time 1). Implementation outcome data, collected from the MCH staff, will be gathered after each group session throughout the two implementation periods. To facilitate coordination and program implementation, participating MCH will be provided with two tablets and a small incentive which could offset implementation costs.

**Table 3 Study Measures for the Evaluation Study: Constructs, Informants, Assessment Schedule, and Assessment Tools.**

| Constructs, Informant, & Assessment Time                                                                                                                                                                                                                                                    | Assessment Tools/Measures                                                                                                                                                                                                                                                                                                               |
|---------------------------------------------------------------------------------------------------------------------------------------------------------------------------------------------------------------------------------------------------------------------------------------------|-----------------------------------------------------------------------------------------------------------------------------------------------------------------------------------------------------------------------------------------------------------------------------------------------------------------------------------------|
| Multi-level D&I Context (domains listed in Figure 1) [Time 1]                                                                                                                                                                                                                    |                                                                                                                                                                                                                                                                                                                                         |
| Inner setting & Individual Characteristics(MCH staff, Adolescent reports): ♦ MCH system characteristics; ♦ Implementer demo & attitude about the EBI; ♦ Family characteristics                                                                                                   | Provider Environment Questionnaire Survey (72, 73); Organization climate/Readiness Questionnaire (107); EBP Attitude Scale ( 74); Family Demographics /social determinants                                                                                                                                           |
| Implementation Outcomes [Assessed Throughout Implementation Period]                                                                                                                                                                                                                  |                                                                                                                                                                                                                                                                                                                                         |
| a) Fidelity (Staff): % of content provided; b) Engagement (staff report): targets' engagement
b) Quality of Implementation(adolescent-report): ♦ Satisfaction;                                                                                                      | a: Fidelity Checklists  . b: Program Engagement; c: Satisfaction  ;                                                                                                                                                                                                                        |
| FBO Pediatric Mental Health Service Outcomes [Time 1, Time 2]                                                                                                                                                                                                                        |                                                                                                                                                                                                                                                                                                                                         |
| a) MCH service quality (adolescent mothers): patient satisfaction; b) MCH climate (staff report): support, trust, communication about adolescent health.                                                                                                                      | a: Service quality; b: Organization Climate Questionnaire)                                                                                                                                                                                                                                                  |
| mhGAP/IPT-G Effectiveness Outcomes[Time 1, Time 2]                                                                                                                                                                                                                                   |                                                                                                                                                                                                                                                                                                                                         |
| a) Adolescent mental health outcomes (Primary) (adolescent report); b) family functioning outcomes (Secondary outcomes) (adolescent & caregiver report): functioning, depression, trauma, adjustment, social support, self-efficacy, stress, family interpersonal communication. | a: WHO-Disability Assessment Schedule; Edinburgh Postpartum Depression Scale; Patient Health Questionnaire-9; b: Self-efficacy; Social support; PTSD Patient Checklist-Civilian; Kessler Psychological Distress Scale; Adolescent Interpersonal Connectedness and Conflict Inventory( 73, 74, 75, 76, 77, 78, 79, 80, 81) |

**Power Calculation.** The sample size (n=90) for the effectiveness evaluation is determined based on medium to large effect size ( $d=.70-1.5$ ) of the IPT intervention reported in the literature based on LMICs (assuming 80% power of two-side significant test with  $\alpha=.05$ ). Because the primary effectiveness outcome (i.e., depression) will be based on adolescent report, we anticipate the group nesting will be very low (ICC close to 0) as evident from my mentors' prior research experience and data reported in the literature. Also, adolescent mental health outcomes will be assessed at 2 time points (at baseline and post intervention). For the estimated sample, we will have adequate power to detect impacts that are meaningful and realistic for the Full G-IPT (medium to large effects). We may not have sufficient power for the mini version of G-IPT (as we anticipate the effect size may be smaller). Given this is a pilot implementation-effectiveness study (with limited research budget), the proposed study will provide data for estimating the size of intervention effect, which will be used to do more accurate power estimation for the R01 application (see Table 3 for the

detectable effect sizes with a range of ICCs).

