**Table 4. Power estimation for the primary effectiveness outcomes (adolescent depression)**

| ICC  | Design effect | Power Estimate for Post Intervention                                |                         |
|------|---------------|---------------------------------------------------------------------|-------------------------|
|      |               | Effective sample Size total
(N* for 1:1 two group
comparison) | Detectable Cohen's
d |
| 0.00 | 1.00          | 60                                                                  | 0.74                    |
| 0.01 | 1.14          | 53                                                                  | 0.78                    |
| 0.03 | 1.42          | 42                                                                  | 0.89                    |
| 0.05 | 1.70          | 35                                                                  | 0.96                    |

*Note. In cluster RCT, the detectable effect sizes depend on the usual study design parameters, cluster sizes and the ICCs. The clustering usually leads to a decrease of the actual sample size (N) by a factor called Variance Inflation Factor (VIF). The effective sample size (N\*) in the cluster RCT is  $N^* = N/VIF$ , where  $VIF = 1 + n(m-1)$ . Estimations of detectable effects reported here consider: 1) ICC (intervention group level) will be small (range from 0 - 0.05); (2) each arm with N of 30, average group size 15; and (3) comparison between mini G-IPT vs. control or between Long G-IPT vs. control (with N of 60 for each pair of comparison).*

**Analysis Plan.** Data collected through 2 cohorts will be analyzed. Hypotheses to be tested include:

- relative to control, pregnant adolescents in the IPT-G will have better outcomes (on Primary and Secondary);
- both IPT-G full and mini versions will be effective, but slightly high impacts for the IPT-G full version; and
- Intervention implementation using task-shifting/sharing approach will have be highly acceptable, engaging, and have high fidelity (for both full and mini versions).

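### Table 3 labels three scales primary, while the design text, alpha and power are set for depression as one endpoint in one comparison, and no depression scale is named as primary

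*Protocol*

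**What the plan says.** The Protocol describes primary effectiveness in several places.

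- **Section 3.5, opening (repeated in the Synopsis under Study Design):** "Primary outcomes will be focus on acceptability, engagement with the interventions, and effectiveness on adolescents' depression". No instrument is named, and functioning or disability is not mentioned.
- **Section 3.5, Table 3, effectiveness block:** the first group is headed "Adolescent mental health outcomes (Primary) (adolescent report" and its tools are "WHO-Disability Assessment Schedule; Edinburgh Postpartum Depression Scale; Patient Health Questionnaire-9". No order is given among the three.
- **Section 3.5, Power Calculation:** "the primary effectiveness outcome (i.e., depression) will be based on adolescent report", with the sample size set "assuming 80% power of two-side significant test with" alpha 0.05. Again no scale is named.
- **Section 3.5, Table 4:** the title is "Power estimation for the primary effectiveness outcomes (adolescent depression". Its note bases the detectable effects on mini against control or full against control, with 60 participants per pair.
- **Section 3.5, Analysis Plan:** the first hypothesis is that "relative to control, pregnant adolescents in the IPT-G will have better outcomes (on Primary and Secondary" sets of outcomes. The second expects both versions to work, the full version slightly better.

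The Power Calculation also calls the study a pilot, whose effect estimate will feed the power calculation of a later application. It warns that power for the mini version may be insufficient.

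**The concern.** WHODAS is a disability scale, so its primary label in Table 3 does not fit text that confines primary effectiveness to depression. Once WHODAS is set aside, two depression scales remain with nothing to say which is primary. If EPDS and PHQ-9 point different ways, the Protocol does not say which result answers the primary question. Nor does it say which scale yields the effect size to be carried forward, which is a stated purpose of the pilot.

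Alpha and power are affected too. Both were set for one outcome in one pairwise comparison, yet the analysis plan tests primary outcomes, in the plural, and expects both active arms to beat control. It does not say whether one primary scale or all of them must show a difference. If one is enough, the error rate over the primary family exceeds 5%. If all three are required, power for that joint result falls below the stated 80% unless the scales are perfectly correlated. Neither reading matches the Power Calculation.

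**Working it through.** **Inputs from the Protocol.** Three arms of 30; two comparisons with control, N = 60 each; two-sided alpha 0.05; 80% power; detectable d = 0.74 at ICC 0 (Table 4); three instruments in the primary group (Table 3).

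**Assumed, because the Protocol does not give them.** Equal correlation r between instruments, varied from 0 to 0.9; no true effect on any scale in either arm (global null); every test unadjusted at two-sided 0.05.

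**Step 1: reproduce the plan's figure.** The normal approximation is d = (z₀.₉₇₅ + z₀.₈₀) × √(4/N) = (1.960 + 0.842) × √(4/60) = 0.723. The two-sample t-test solution with 30 per arm is d = 0.736, which agrees with the stated 0.74. Power at d = 0.74 is 80.5%. The figure is therefore right for one endpoint in one comparison.

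**Step 2: count the tests.** Three scales × two comparisons = 6. If all six were independent, P(at least one p < 0.05) = 1 − 0.95⁶ = 26.5%. That is too high here, because both comparisons share the control arm and the scales are likely to be correlated.

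**Step 3: simulate with the shared control.** For each scale, Z_full = (A − C)/√2 and Z_mini = (B − C)/√2, where A, B and C are the standardised arm means (full, mini, control), correlated r across scales. There were 400,000 to 600,000 draws. P(at least one false positive):

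| r between scales | 3 scales, 6 tests | 3 scales, benefit direction only | 2 depression scales, 4 tests |
|---|---|---|---|
| 0 | 24.8% | 12.9% | 17.3% |
| 0.3 | 23.7% | 12.1% | 16.8% |
| 0.5 | 22.0% | 11.0% | 16.2% |
| 0.7 | 19.2% | 9.6% | 14.8% |
| 0.9 | 14.8% | 7.5% | 12.6% |

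One scale with two comparisons gives 9.1% two-sided. A check with t-tests on 30 per arm agreed for the three-scale case: 25.2% at r = 0, 21.6% at 0.5 and 19.6% at 0.7.

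**Step 4: effect on the detectable difference.** With one scale and alpha split over the two comparisons (0.025 each), the detectable d is 0.814, and power at d = 0.74 is 71%. With alpha split over all six tests (0.05/6 each), the detectable d is 0.926 and power at d = 0.74 is 56%.

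**The case against.** A reader might infer more than the Protocol supports in four ways.

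- **Three rival primary sets.** The Power Calculation speaks of the primary *effectiveness* outcome. In a hybrid effectiveness-implementation design, that is the effectiveness part of the list opening section 3.5, alongside acceptability and engagement. Those two passages agree. The contradiction is the WHODAS entry in Table 3; the open choice between EPDS and PHQ-9 is an ambiguity.
- **A flat false-positive rate of about 20%.** That figure needs between-scale correlations near 0.65, the global null and six unadjusted tests. The Protocol gives no correlations and never specifies six tests. A two-sided rate also counts apparent harm, so the benefit-only figures fit a worry about claiming success better.
- **A missing multiplicity rule as an error.** Alpha allocation and test order are commonly left to the SAP, which is not at hand. Their absence is not the finding.
- **Success claimed on whichever scale is significant.** The Protocol states no success criterion. It calls the study a pilot and its effectiveness aim preliminary.

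These objections narrow the point and lower its weight. They do not remove it. The Protocol still lists hypotheses to be tested, states a two-sided alpha and claims adequate power for the full version. The conflict over the primary label lies within the Protocol itself, so an SAP could not follow every passage as written.

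**Conclusion.** The point holds as an inconsistency in the primary effectiveness endpoint. Table 3 gives primary status to a disability scale and two unranked depression scales, while section 3.5 and Table 4 confine primary effectiveness to depression and set power for one endpoint in one comparison.

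The size depends on how the plan is read. Six unadjusted two-sided tests under the global null give about 15% to 25% over the assumed correlations, or about 7% to 13% counting only false positives in favour of treatment. If the depression-only wording governs, the two scales give about 13% to 17%. One scale in both comparisons gives 9%. Every two-sided figure is above 5%, but none is a property of the Protocol alone. Given the pilot purpose, this should be fixed but does not block the trial.

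**What to change.** Name one depression scale at Time 2, adjusted for its own baseline, as the single primary effectiveness endpoint. Use the same wording in the opening of section 3.5, Table 3, the Power Calculation and the matching Synopsis sentence. EPDS is a natural choice because the inclusion criteria in section 3.7 already use it for screening, although DSM-IV-TR criteria are an alternative route to entry. PHQ-9 would be equally coherent if the sponsor prefers it and says so.

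Move WHODAS and the other depression scale to secondary. Keep acceptability and engagement as implementation outcomes.

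Add to Table 4 that its power applies to one comparison at two-sided 0.05, and that the detectable d at ICC 0 becomes 0.81 if alpha is split over the two comparisons with control. Whether to order the comparisons, split alpha or treat one as exploratory is the sponsor's choice and may sit in the SAP.

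The cost is Protocol wording and the loss of primary status for two scales. Assessments and sample size do not change.

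### The Power Calculation claims 80% power from d = 0.70, but the protocol's own Table 4 shows that 30 versus 30 detects no effect smaller than d = 0.74, before any loss to follow-up

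*Protocol*

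**What the plan says.** The Power Calculation paragraph of section 3.5 (Methodology for Aim 3) says: "The sample size (n=90) for the effectiveness evaluation is determined based on medium to large effect size". It gives the range as d = 0.70 to 1.5 and the operating characteristics as "assuming 80% power of two-side significant test" at alpha 0.05. On clustering it says "we anticipate the group nesting will be very low (ICC close to 0"). It then concludes that "we will have adequate power to detect impacts that are meaningful and realistic for the Full G-IPT (medium to large effects"). It concedes that power may be insufficient for the mini version, calls the study a pilot, and refers the reader to Table 3 for detectable effects.

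Randomisation is to three arms, "n=30 for each arm". Table 4, headed "Power estimation for the primary effectiveness outcomes (adolescent depression"), lists detectable Cohen's d of 0.74, 0.78, 0.89 and 0.96 at ICC 0, 0.01, 0.03 and 0.05. Its note takes an average group size of 15 and works "with N of 60 for each pair of comparison".

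The Analysis Plan in the same section models the post-intervention outcome with its baseline value as a covariate.

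**The concern.** The paragraph and the table describe the same comparison and disagree. The paragraph puts the lower end of the effects covered at 80% power at 0.70. The table's most favourable row starts at 0.74, and the others are further away. The cross-reference to Table 3, which is the table of study measures, makes the mismatch easy to miss.

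Table 4 also enters all 60 randomised participants of each pair, although Time 2 falls about 3-4 months after baseline. Some loss is plausible in that interval, and neither the paragraph nor the table allows for it.

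Effectiveness on adolescent depression is a named primary outcome, and superiority over control is a stated hypothesis. The full version against control is the comparison the protocol singles out as adequately powered, so the concessions about the mini version do not cover it. A reader who trusts the paragraph would give a null result more weight against d = 0.70 than the printed calculation justifies.

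**Working it through.** **Inputs from the protocol.** 30 per arm and 60 per pair; two-sided alpha 0.05; power 80%; d = 0.70 as the lower bound; ICC 0 to 0.05; group size 15 in Table 4. Operational Definitions puts an IPT group at 6-8.

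**Inputs assumed, because the protocol gives none.** Loss of 10% or 20%; baseline-to-post correlation r of 0.3 to 0.5.

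**Method.** Two-sample t-test with the noncentral t distribution. For n per arm, df = 2n − 2 and noncentrality = d × √(n/2). Clustering enters as in Table 4: effective N = 60 / VIF, with VIF = 1 + ICC × (15 − 1).

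**Step 1: reproduce Table 4, then read off power at d = 0.70.**

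| ICC | VIF | Effective N | Detectable d, Table 4 | Detectable d, recomputed at that N | Power at d = 0.70 |
|---|---|---|---|---|---|
| 0 | 1.00 | 60 | 0.74 | 0.736 | 76.0% |
| 0.01 | 1.14 | 53 | 0.78 | 0.785 | 70% |
| 0.03 | 1.42 | 42 | 0.89 | 0.886 | 60% |
| 0.05 | 1.70 | 35 | 0.96 | 0.976 | 52% |

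The table reproduces. The last row's 0.96 corresponds to rounding up to 18 per arm. The fault is therefore in the paragraph's lower bound, not in the table.

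**Step 2: what d = 0.70 would need.** At n = 30 the noncentrality is 0.70 × √15 = 2.71 on 58 df, which gives 76.0% (77.4% by the normal approximation). By the t-test 33 per arm gives 79.97%, so 34 per arm are needed, or 3 × 34 = 102 in total. The normal approximation gives 33 per arm, or 99. Both exceed 90.

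**Step 3: group size at ICC 0.05.**

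- Groups of 6: VIF = 1 + 0.05 × 5 = 1.25, effective N = 48, power at 0.70 = 66%.
- Groups of 8: VIF = 1 + 0.05 × 7 = 1.35, effective N = 44.4, power at 0.70 = 63%.
- Groups of 15 with clustering in the IPT arm only: effective sizes 30/1.70 = 17.6 versus 30, power at 0.70 = 63%.

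**Step 4: loss to follow-up, ICC 0, unadjusted.**

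- 10% loss: 27 per arm, detectable d = 0.78, power at 0.70 = 71%.
- 20% loss: 24 per arm, detectable d = 0.83, power at 0.70 = 66%.

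**Step 5: baseline adjustment, ICC 0.** Adjustment multiplies the detectable d by √(1 − r²).

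| r | Power at d = 0.70, complete data | Detectable d, complete data | Detectable d, 20% loss |
|---|---|---|---|
| 0.3 | 79.8% | 0.70 | 0.79 |
| 0.4 | 82.9% | 0.67 | 0.76 |
| 0.5 | 86.8% | 0.64 | 0.72 |

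The correlation that brings the detectable d to 0.70 is √(1 − (0.70/d₀)²), where d₀ is the unadjusted detectable effect. This gives 0.31 with complete data (d₀ = 0.736), 0.43 with 10% loss (d₀ = 0.777) and 0.53 with 20% loss (d₀ = 0.826).

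**The case against.** The case on the other side has four parts.

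- **Baseline adjustment.** A reader might infer that 76% is the most the design can deliver. The documents do not support that. It is the ceiling of the unadjusted Table 4 calculation, whereas the Analysis Plan fixes a baseline-adjusted model, which would reach about 80% at d = 0.70 with a correlation just above 0.3, ICC 0 and full retention. This stands. But the protocol states no correlation and takes no credit for one in its power figures, and the correlation needed rises once participants are lost.
- **The extreme row.** A reader might take 52% as the trial's power. It comes from the last row of a sensitivity table, while the plan expects an ICC near 0. It also rests on groups of 15 clustered in both arms, although Operational Definitions says 6-8 and controls receive standard care. This stands: at the expected ICC the unadjusted shortfall is about 4 percentage points.
- **Disclosure.** Table 4 prints the limits openly, and the text admits pilot status and weak power for the mini version. This lowers the seriousness of the point. It does not make the sentence about 0.70 agree with the table.
- **Scope.** A reader might criticise power at d = 0.50, or say that these power figures will carry into the next grant. Neither follows. The protocol's own medium-to-large range starts at 0.70, and what it passes on to the R01 application is the effect estimated from the trial's data.

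**Conclusion.** The lower bound of d = 0.70 at 80% power is not supported by the protocol's own calculation. For 30 versus 30, unadjusted and with complete data, the detectable effect is 0.74 at ICC 0 and 0.96 at ICC 0.05. A true effect of 0.70 would be missed in about 24% of trials rather than 20% at the expected ICC, and more often with clustering or loss.

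The gap is confined to the bottom of the claimed range. At d = 1.0, unadjusted power with complete data is 97% at ICC 0 and 82% at ICC 0.05. Whether the planned analysis would in fact reach 80% at 0.70 cannot be settled, because it depends on a correlation and a retention rate that the protocol does not give. The documents therefore do not show that the trial is too small for its purpose. They show a stated figure that needs a modest correction.

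**What to change.** Keep n = 90. In the Power Calculation paragraph, replace the 0.70 lower bound and bring the adequacy sentence for the full version into line, in one of two ways:

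- **Unadjusted.** For example: 80% power for d of 0.74 or more with complete data and ICC 0; for d of 0.78 to 0.83 or more with an assumed 10-20% loss; higher with clustering, as in Table 4.
- **Adjusted.** Restate the detectable effect for the baseline-adjusted model, giving the assumed baseline-to-post correlation and loss rate. This matches the planned analysis more closely and may be more favourable than the unadjusted figure.

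Also point the text to Table 4 instead of Table 3.

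The cost is wording only. Sample size, allocation, outcomes and analysis do not change. The unadjusted option makes the stated detectable effect slightly less favourable than the text now claims.
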